### Recruitment procedures

All participants will be recruited from the Department of Rehabilitation Medicine, Guangdong Sanjiu Brain Hospital. The recruitment process follows a three-step procedure: first, potential participants will be identified through referrals from neurologists, rehabilitation specialists, and the hospital’s internal referral network, with eligibility screening based on medical record review and preliminary clinical assessment; second, eligible candidates will be contacted by a research coordinator, who will provide their legally authorized representatives with a detailed explanation of the study objectives, procedures, risks, and benefits, and written informed consent will be obtained; finally, enrolled participants will undergo a comprehensive baseline assessment—including demographic characteristics, detailed medical history, current clinical status (CRS-R score), neuroimaging investigations, and laboratory testing—conducted collaboratively by the research team comprising neurologists, rehabilitation therapists, and research nurses.

### Variables

#### Primary and secondary outcome variables

The primary outcome variables of this study are as follows: (1) pDoC recovery, defined as emergence from MCS (eMCS), operationalized as achieving a CRS-R communication subscale score ≥2 (functional interactive communication) or a motor subscale score ≥6 (functional object use), confirmed on ≥2 standardized CRS-R assessments conducted ≥7 days apart and sustained for ≥4 consecutive weeks. This criterion applies uniformly to patients with a baseline diagnosis of VS or MCS. All recovery determinations will be adjudicated by the independent Endpoint Adjudication Committee; (2) all-cause mortality, defined as death from any cause at any point during the 5-year follow-up period (up to and including month 60). In the competing-risk analytical framework, all-cause mortality serves as the primary competing risk event for the consciousness recovery outcome. Patients who survive to the end of the 60-month follow-up without having achieved the consciousness recovery endpoint will be administratively right-censored at month 60; and (3) major cardiovascular events (MACE), encompassing myocardial infarction (defined in accordance with the Fourth Universal Definition of Myocardial Infarction, requiring elevated cardiac biomarkers in conjunction with clinical evidence of myocardial ischemia), hospitalization for heart failure (defined as inpatient admission requiring intravenous diuretics or inotropic support), and stroke (confirmed by neuroimaging [CT/MRI] with neurological deficits persisting for more than 24 h).

Secondary outcome variables include: (1) changes in functional status, assessed using the Glasgow Outcome Scale–Extended (GOS-E) and the Disability Rating Scale (DRS) (8, 9); (2) dynamic changes in biomarkers, including serum neurofilament light chain (NfL), glial fibrillary acidic protein (GFAP), S100 calcium-binding protein B (S100B), and other injury- and recovery-related biomarkers; (3) health-related quality of life, evaluated using the EQ-5D questionnaire, with caregiver proxy responses employed when direct patient assessment is not feasible; and (4) rehospitalization rate, documented by recording the frequency and causes of readmission, with particular attention to common complications such as infections, seizures, and respiratory events.

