### Follow-up procedures

Follow-up assessments will employ a hybrid surveillance strategy combining in-person evaluations with remote monitoring. Core neurobehavioral and functional assessments (CRS-R, GOS-E, DRS, EQ-5D, SF-36, FIM, HADS, and Zarit Caregiver Burden Interview) will be conducted at bedside by certified assessors at baseline and at 3, 6, 12, 24, 36, 48, and 60 months (8 assessment timepoints in total, comprising 7 in-person follow-up visits). The Chinese validated CRS-R (7) will be used throughout. Assessors must complete standardized training—covering scoring, ≥10 supervised assessments, and ICC ≥ 0.85 reliability—before independent use. The same assessor will evaluate each participant at all timepoints when feasible; if replaced, inter-rater reliability will be verified against the prior assessor’s last two evaluations. Total and subscale scores will be recorded at each visit. eMCS is defined by subscale-specific behavioral thresholds (per Primary Outcome Variables), not a total score of 23/23, which reflects full neurological recovery rather than functional communication or object use. Neuroimaging investigations (MRI/DTI/fMRI) and serum biomarkers (NfL, S100B, GFAP, and other injury-related biomarkers) will be performed at baseline and at 6, 12, 24, 36, 48 and 60 months. Following the 6-month visit, remote follow-ups will be conducted by telephone interview supplemented by caregiver-reported outcomes at 3-month intervals between scheduled in-person visits, primarily capturing vital status, rehospitalization events, and major adverse events. Remote follow-ups will be administered by uniformly trained research coordinators using standardized scripts, with video calls employed as an adjunct to confirm the patient’s general condition. In-person outpatient visits will be conducted by neurologists and rehabilitation therapists.

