Follow-up assessments will capture: changes in consciousness level (CRS-R); vital status; major cardiovascular events; functional independence (Functional Independence Measure [FIM]); health-related quality of life (SF-36); caregiver burden (Zarit Caregiver Burden Interview); changes in medication or treatment regimens; activities of daily living (ADLs) and instrumental activities of daily living (IADLs); mental health status (Hospital Anxiety and Depression Scale [HADS]); and adverse event documentation. All follow-up data will be entered in real time into an electronic data capture (EDC) system, with monthly data quality reviews conducted to achieve a target follow-up completion rate of ≥ 85%.

Outcome event ascertainment procedures are as follows: recovery status will be confirmed through a composite of clinical assessments, medical record review, and neuroimaging evidence (e.g., fMRI or EEG demonstrating improved cortical activity); death events will be ascertained via civil death registration systems, family-reported notification, and hospital records, with cause-specific mortality classified as neurological deterioration, cardiovascular events, infection, or other causes; cardiovascular events will be adjudicated according to internationally accepted definitions supported by neuroimaging and laboratory evidence. Telephone interviews have been established as a feasible follow-up modality, demonstrating agreement with self-reported outcome measures in the majority of settings, achieving a cohort retention rate of 93% within 6 months in culturally adapted intervention research, and proving applicable to the longitudinal assessment of functional and cognitive recovery trajectories following neurological infections (12) (Table 1).

**Table 1 tab1:** Evaluation parameters at baseline and follow-up visits.

Evaluation parameter	Baseline (enrollment)	Follow-up (telephone/video or on-site visits)						
	(Hospital admission)	Visit 1 (3 m)	Visit 2 (6 m)	Visit 3 (12 m)	Visit 4 (24 m)	Visit 5 (36 m)	Visit 6 (48 m)	Visit 7 (60 m)
Informed consent	x							
Inclusion criteria met	x							
Demographics & medical history	x							
Vital signs & neurological exam	x							
Consciousness level (CRS-R)	x	x	x	x	x	x	x	x
Functional status (GOS-E, DRS)	x	x	x	x	x	x	x	x
Quality of life (EQ-5D)	x	x	x	x	x	x	x	x
Survival status	x	x	x	x	x	x	x	x
Rehospitalization & complications	x	x	x	x	x	x	x	x
Adverse events	x	x	x	x	x	x	x	x

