### Loss to follow-up

A standardized definition of loss to follow-up will be applied (three consecutive missed follow-up contacts). Data from participants lost to follow-up will be right-censored at the time of their last valid contact. Reasons for loss to follow-up (relocation, withdrawal, death, loss of contact, etc.) will be systematically documented. Baseline demographic and clinical characteristics will be compared between participants lost to follow-up and those who complete follow-up to assess potential selection bias. Inverse probability weighting (IPW) will be applied as needed to statistically correct for informative censoring due to dropout, thereby enhancing the external validity and generalizability of study findings.

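### The recovery endpoint does not fit the CRS-R schedule, and the planned censoring and Fine-Gray analysis make no allowance for visit gaps of up to 12 months

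*Protocol article*

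**What the plan says.** **Endpoint** (Primary and secondary outcome variables). Emergence is defined by CRS-R communication or motor subscale thresholds, "confirmed on ≥2 standardized CRS-R assessments conducted ≥7 days apart and sustained for ≥4 consecutive weeks", and is adjudicated by a committee. Survivors without recovery are censored at month 60. Death is the competing event.

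**CRS-R schedule** (Follow-up procedures). Core assessments, including CRS-R, are done at the bedside "at baseline and at 3, 6, 12, 24, 36, 48, and 60 months (8 assessment timepoints in total, comprising 7 in-person follow-up visits"). Table 1 marks CRS-R at the same points, although its column header reads "Follow-up (telephone/video or on-site visits").

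**Remote contacts** (Follow-up procedures). After month 6, calls take place "at 3-month intervals between scheduled in-person visits", "primarily capturing vital status, rehospitalization events, and major adverse events". Video is an adjunct for checking general condition.

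**A second confirmation route** (Follow-up procedures, outcome ascertainment). Here recovery is confirmed by a composite of clinical assessment, medical records and imaging or EEG evidence. Deaths come from civil registration, family notification and hospital records.

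**Analysis** (Primary analysis). Cumulative incidence functions and a Fine-Gray model, with recovery as the event of interest and death as the competing event.

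**Loss to follow-up.** Defined as "three consecutive missed follow-up contacts". The censoring rule is: "Data from participants lost to follow-up will be right-censored at the time of their last valid contact". The section adds: "Reasons for loss to follow-up (relocation, withdrawal, death, loss of contact, etc.) will be systematically documented".

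**The concern.** The endpoint rule needs at least two CRS-R assessments and four weeks of persistence, but the schedule provides a single time point every 3 to 12 months. Three things follow.

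1. **Confirmation.** The article does not say which assessment confirms a first positive CRS-R. It gives a different, composite route elsewhere. After month 60 there is no visit left.
2. **Timing.** Recovery is observed only on the visit grid, while deaths come from sources that do not depend on the visits. Someone who emerges and dies between two visits is counted as dead without recovery. Detected recoveries are dated late.
3. **Censoring.** For a participant lost to follow-up, the last valid contact may be a call that was not designed to assess consciousness. The time between the last CRS-R and that call enters the recovery analysis as observed, recovery-free time.

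All three push the estimated five-year recovery incidence down or recovery times late, for the first-listed primary outcome. The Discussion also presents the critical time windows of recovery as something the design can characterise; annual visits after month 12 limit that.

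**Working it through.** **Schedule.** The gaps between CRS-R time points are 3, 3, 6, 12, 12, 12 and 12 months. The shortest is 3 months, so no scheduled assessment falls within four weeks of another. Four of the seven gaps are 12 months. Calls fall at months 9, 15, 18, 21, 27, 30, 33, 39, 42, 45, 51, 54 and 57 (13 contacts).

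**Month 60.** A first positive score at month 60 needs a second CRS-R at least 7 days later and four weeks of persistence. Both lie beyond the censoring date.

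**Censoring example.** Last CRS-R at month 12, calls answered at 15, 18 and 21, then month 24, 27 and 30 contacts missed. Censoring is at month 21, so 21 − 12 = 9 months count as recovery-free without an assessment of consciousness.

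**The plan's rate.** The sample size section gives 34% at five years and 8% per year: 1 − 0.92^5 = 34.1%, which reproduces. The plan calls the 34% a cumulative incidence in a competing-risk framework, so I keep it as the incidence after allowing for deaths.

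**Model.** Monthly recovery hazard λ and death hazard μ are constant, and recovery persists once reached.
- μ = −ln(1 − annual mortality)/12. Annual mortality of 5, 10 and 20% is assumed; the article gives no figure.
- λ solves λ/(λ+μ) × [1 − exp(−60(λ+μ))] = 0.34.
- Recovered in the visit interval (a, b] and alive at b: [exp(−λa) − exp(−λb)] × exp(−μb), summed over the seven intervals.

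| Assumed annual mortality | 5% | 10% | 20% |
|---|---|---|---|
| μ per month | 0.00427 | 0.00878 | 0.01860 |
| λ per month | 0.00801 | 0.00928 | 0.01251 |
| Recovery incidence, true | 0.3400 | 0.3400 | 0.3400 |
| Seen at a CRS-R visit | 0.3327 | 0.3254 | 0.3114 |
| Recoverers dying before any CRS-R (1 − seen/true) | 2.1% | 4.3% | 8.4% |
| Mean delay to first positive CRS-R, months | 5.1 | 4.9 | 4.6 |
| First seen at month 60, share of detected | 14.5% | 12.3% | 8.1% |

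**Conditional case.** If confirmation had to wait for the next scheduled visit, exp(−μb) becomes exp(−μc), with c the following visit, and the month-60 interval drops out. Confirmed incidence is then 0.2716, 0.2602 and 0.2371, a loss of 20.1, 23.5 and 30.3% of recoveries.

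**Earlier recovery.** If 50 to 70% of recoveries fall in year 1 (no deaths), the mean detection delay is 4.1 to 3.4 months and 12.5 to 7.5% are first seen at month 60.

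**VS versus MCS.** I took a recovery hazard of 8% per year in one group and 1.3 times that in the other, and compared the ratio of −ln(1 − incidence) at month 60, true against as first seen.

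| Annual mortality, lower- vs higher-recovery group | True | As first seen |
|---|---|---|
| 10% vs 10% | 1.287 | 1.285 |
| 10% vs 5% | 1.49 | 1.52 |
| 20% vs 10% | 1.69 | 1.77 |
| 20% vs 5% | 1.95 | 2.10 |

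The shift is close to nil with equal mortality, about 2 to 5% in the middle rows and about 8% in the last.

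**The case against.** The strongest reply is that the article counts assessment time points and does not limit how many CRS-R administrations one may contain. Its own endpoint rule asks for at least two, a committee adjudicates each recovery, and triggered repeat visits are the sort of detail a condensed article leaves to the full protocol. This largely stands. A reader might infer that recovery can never be confirmed; the documents do not support that, because unscheduled repeats are not forbidden. The month-60 problem remains even with repeats, and so do the two differing confirmation routes.

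Other stronger readings also fail:

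- **A fifth to a third of recoveries will be lost.** The 20 to 30% figures need a rule that confirmation waits for the next scheduled visit. No section states one.
- **Seven days conflicts with four weeks.** Both are minimums that apply together; two assessments four weeks apart are compatible with both.
- **Patients in general are censored at phone calls.** Only those lost to follow-up are. Completers are censored at month 60, an in-person CRS-R visit.
- **Deaths will be coded as loss to follow-up.** Death there is one item in a list of recorded reasons. The outcome and primary analysis sections make it the competing event.
- **The VS versus MCS comparison is invalidated.** The shifts above are small unless mortality differs strongly.

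It can also be said that event dating and interval censoring belong in a SAP. Their absence alone would be no finding. But the article itself fixes the model and the censoring rule, and followed as written they produce the problem. The inverse probability weighting it offers addresses informative dropout; it does not change which time is counted as recovery-free.

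**Conclusion.** The point holds as a mismatch between endpoint, schedule and analysis, and should be fixed. The endpoint's confirmation and persistence requirements are not provided for by the scheduled assessments, and a first positive at month 60 has no route to confirmation before censoring. The Fine-Gray analysis does not allow for recovery being observed only on a grid with gaps of up to 12 months. The censoring rule counts unassessed time as recovery-free in the minority lost to follow-up.

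The size is moderate: about 2 to 8% of recoveries misclassified as the competing event, recovery dated about 5 months late, and roughly 8 to 14.5% of detected recoveries of uncertain status at month 60. These figures rest on constant hazards, persistent recovery, the plan's 34% incidence and assumed mortality of 5 to 20% per year. Earlier recovery would shorten the delay and reduce the month-60 share.

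**What to change.** 1. **Censor recovery at the last CRS-R**, not at the last contact of any kind. Vital status from calls and registries still serves the mortality outcome. This is a wording change.
2. **Analyse recovery as interval-censored or on the visit grid**, for example with a grouped-time complementary log-log subdistribution model, at least as a prespecified sensitivity analysis. It uses data already planned, at the cost of somewhat more analysis work and possibly wider intervals.
3. **Reconcile the endpoint definition with the follow-up schedule and the composite ascertainment route.** State which assessment confirms recovery and how a first positive at month 60 is classified, or reword the rule to what scheduled visits can show. If a repeat CRS-R is chosen, it is needed only for patients with a first positive score: about 311 to 333 per 1,000 in the model above, before loss to follow-up. Rewording needs no visits but changes a primary endpoint, so it is best done before enrolment opens in June 2026.
4. **Wording clean-up.** Remove death from the loss-to-follow-up reasons, since it is the competing event, and align the Table 1 header with in-person CRS-R.

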#### Exposure variable

The primary exposure variable is the baseline level of consciousness (VS or MCS) at enrollment. All enrolled participants will receive standardized multimodal rehabilitation care in accordance with the Chinese Expert Consensus on the Diagnosis and Treatment of Prolonged Disorders of Consciousness (Standard of Care, SOC) (10), encompassing: (1) pharmacological arousal-promoting therapy (e.g., amantadine, donepezil, zolpidem); (2) multimodal sensory stimulation therapy (auditory, tactile, visual, and olfactory modalities); (3) physical therapy (including tilt-table training and passive mobilization); (4) occupational therapy; (5) speech-language therapy; (6) hyperbaric oxygen therapy (where indicated and available); and (7) neuromodulation techniques (e.g., median nerve electrical stimulation, repetitive transcranial magnetic stimulation, spinal cord stimulation), as well as evidence-based complication management (infections, spasticity, pressure injury). Treatment intensity for each modality will be quantified as total weekly contact time (minutes per week) and session frequency, recorded prospectively in the electronic data capture system at each assessment timepoint. All treatment variables will be incorporated as time-dependent covariates (operationalized as weekly contact time (min/week) per rehabilitation modality) in the analytical models to distinguish the natural disease course from treatment-mediated effects.

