### Study objectives

This study aims to systematically characterize the 5-year natural history of pDoC through a prospective cohort design, thereby bridging the critical evidence gap stemming from the absence of large-scale, long-term follow-up investigations. The specific objectives are as follows:To determine the rates of consciousness recovery, all-cause mortality, and major cardiovascular events over a 5-year follow-up period in patients stratified by initial level of consciousness (VS, MCS−, and MCS+); primary comparisons will be conducted at the VS vs. MCS level, with MCS − vs. MCS + differentiation examined in prespecified subgroup analyses.To identify etiology, injury severity (GCS at admission), time from injury to enrollment, Coma Recovery Scale–Revised (CRS-R) subscale profiles, and neuroimaging indices as independent predictors of consciousness recovery and unfavorable outcomes.To develop and validate a multimodal prognostic prediction model integrating clinical, neuroimaging, and biomarker data.

The primary research question of this study is: among patients with prolonged disorders of consciousness (VS or MCS ≥ 28 days post-acute brain injury), does baseline consciousness level (VS vs. MCS) independently predict 5-year consciousness recovery trajectory, after adjustment for etiology, injury severity, and neuroimaging characteristics?

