### Primary analysis

For the primary outcome of consciousness recovery, a competing-risk analytical framework will be applied, in which consciousness recovery is designated as the event of interest and all-cause mortality as the competing risk event. Cumulative Incidence Functions (CIFs) will be estimated, and the Fine-Gray subdistribution hazard model will be used to assess the influence of each predictor on the subdistribution hazard of recovery. For the single-endpoint outcome of all-cause mortality, Cox proportional hazards regression will be employed. Covariates will be introduced in a stepwise fashion across five models: Model 1 (unadjusted); Model 2 (adjusted for demographic variables: age and sex); Model 3 (Model 2 plus clinically relevant injury-related variables: etiology [TBI vs. HIE vs. cerebrovascular vs. metabolic/toxic encephalopathy vs. other], GCS at acute admission, and time from injury to enrollment); Model 4 (Model 3 plus baseline CRS-R total score and neuroimaging indices [DTI-FA and fMRI-DMN connectivity]); and Model 5 (fully adjusted model incorporating all prespecified covariates: age, sex, educational level, comorbidities, etiology of brain injury, GCS at acute admission, time from injury to enrollment, baseline CRS-R total score, and neuroimaging indices). Covariate selection will be guided by directed acyclic graph (DAG) construction and prior literature evidence to avoid bias introduced by over-adjustment of mediators and colliders.

The proportional hazards assumption will be tested using Schoenfeld residuals and log–log survival plots; violations will be addressed through stratified Cox models, time-varying covariates, or restricted cubic splines. Results will be expressed as hazard ratios with 95% confidence intervals. Kaplan–Meier curves will be used to visualize survival probabilities across exposure groups, and forest plots will be employed to display effect estimates and their trends across adjusted models.

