The choice of a prospective cohort design was deliberate and methodologically grounded. Prospective cohort design is the recognized standard for pDoC natural history and prognostic investigation, as reflected by all landmark studies cited in this protocol (13–17). More fundamentally, the Fine-Gray competing-risk model—a core analytical feature of this protocol—requires prospectively ascertained event-time data and is methodologically incompatible with a retrospective case–control framework. The prospective design additionally enables modeling of time-dependent covariates (notably, treatment intensity) to distinguish natural recovery trajectories from treatment-mediated change, and uniquely permits characterization of the temporal dynamics of recovery—information that is inaccessible to case–control designs. Nevertheless, to address the analytical goal of comparing patients who recover with those who do not, a pre-specified nested comparison between recovery-positive and recovery-negative groups will be conducted within the cohort framework using the Fine-Gray model with pre-specified clinical prognostic predictors.

The 5-year follow-up horizon was selected to align with the most comprehensive existing prospective pDoC cohorts (13, 15) reporting 5-year cumulative recovery rates of 42.3–48.7% in Chinese populations, and to capture late recovery events beyond the conventional 12-month observation window that dominates prior literature.

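### The article says both that post-baseline therapy time enters the models and that the recovery models contain no treatment term; inside a Fine-Gray model, therapy time has no defined value after death

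*Protocol article*

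**What the plan says.** The Exposure variable section sets the exposure: "The primary exposure variable is the baseline level of consciousness (VS or MCS) at enrollment". It then says of therapy that "All treatment variables will be incorporated as time-dependent covariates (operationalized as weekly contact time (min/week) per rehabilitation modality) in the analytical models", with the purpose "to distinguish the natural disease course from treatment-mediated effects". Therapy time is "recorded prospectively in the electronic data capture system at each assessment timepoint", and Table 1 shows treatment records at baseline and at every follow-up visit to month 60. The Discussion, just after presenting Fine-Gray as central to the design, says that the prospective design "enables modeling of time-dependent covariates (notably, treatment intensity) to distinguish natural recovery trajectories from treatment-mediated change".

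The Primary analysis section makes death the competing event and says that "the Fine-Gray subdistribution hazard model will be used to assess the influence of each predictor". Its Models 1 to 5 hold baseline variables only. Model 5 is presented as the complete adjustment set, yet it names no treatment variable. Covariates are to be chosen with a DAG "to avoid bias introduced by over-adjustment of mediators and colliders". The primary question under Study objectives asks whether VS versus MCS predicts recovery "after adjustment for etiology, injury severity, and neuroimaging characteristics"; treatment is not in that list.

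**The concern.** Two rules in the same article point in different directions. One puts all treatment variables into the models without limiting which models. The other lists the recovery models without treatment. Two analysts could each follow the text and report different VS/MCS estimates.

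The treatment rule also has two technical problems if it is applied to the Fine-Gray models. First, follow-up therapy minutes are measured after the exposure and may depend on it and on the patient's evolving state. Ordinary adjustment for such a variable does not reliably separate natural course from treatment-mediated change. It removes whatever part of the exposure effect passes through therapy, and it can add bias where evolving state drives both therapy and recovery. Second, therapy time exists only while the patient is alive, whereas Fine-Gray keeps patients who died in the risk set for recovery.

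**Working it through.** **1. The statements side by side.**

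| Place in the article | Treatment in the recovery model? |
|---|---|
| Exposure variable | Yes: all treatment variables, time-dependent, models not named |
| Discussion (design rationale) | Yes: treatment intensity, time-dependent |
| Study objectives (primary question) | Not listed |
| Primary analysis, Models 1–5 | Not listed, including the fully adjusted model |
| Primary analysis, nested comparison | Not listed |
| Prediction model | Not listed |
| Primary analysis, DAG rule | Argues against adjusting for mediators |

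No section confines the time-dependent terms to a cause-specific or secondary model, or says what value therapy time takes after death.

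**2. The plan's own effect size.** The plan gives no figure for therapy, so its design hazard ratio of 1.3 serves as the reference. With two-sided α = 0.05, 80% power and 30% exposed, Schoenfeld's formula gives (1.960 + 0.842)² / (0.30 × 0.70 × (ln 1.3)²) = 542.97, or 543 events. The article states 544, so the inputs reproduce.

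**3. Shift from adjusting for a mediator.** Take the HR as MCS versus VS. As an approximation, adjusted HR = total HR / exp(β × Δ). Here Δ is the MCS minus VS difference in weekly therapy minutes and β is the log-HR per minute. Both are assumptions; β = 0.10/30 throughout.

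| Δ (min/week) | exp(β × Δ) | Adjusted HR from 1.30 |
|---|---|---|
| 0 | 1.000 | 1.30 |
| +30 | exp(0.10) = 1.105 | 1.30/1.105 = 1.18 |
| +60 | exp(0.20) = 1.221 | 1.30/1.221 = 1.06 |
| −60 | exp(−0.20) = 0.819 | 1.30/0.819 = 1.59 |

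**4. The value after death.** A small simulation used assumed inputs: 30% exposed, direct HR 1.3, 5-year recovery about 30–34%, therapy updated at the planned visit times, deaths kept in the risk set to month 60, no other censoring, and two runs of 2,500 patients per scenario. Therapy has an SD of about 0.7 units, so differences of 0.5 and 1 unit are about 0.7 and 1.4 SD. Each row gives the exposure's subdistribution HR from the same data.

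| Therapy difference (units) | log-HR of therapy per unit | No therapy term | Last value carried past death | Low 'zero' value after death |
|---|---|---|---|---|
| 0 | 0.2 | 1.28 | 1.28 | 1.25 |
| 0 | 0.4 | 1.41 | 1.41 | 1.38 |
| 0.5 | 0.2 | 1.50 | 1.35 | 1.16 |
| 0.5 | 0.4 | 1.57 | 1.29 | 1.14 |
| 1.0 | 0.2 | 1.65 | 1.35 | 1.04 |
| 1.0 | 0.4 | 1.99 | 1.35 | 1.10 |

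Differences between rows carry simulation noise: about 1,500 events per scenario give a standard error of roughly 1/√(1,500 × 0.21) = 0.056 on the log scale. The comparison within a row is the relevant one. Where therapy differs by baseline level, the coding convention alone moves the estimate from 1.29–1.35 to 1.04–1.16.

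A cause-specific model needs no value after death. In the four rows with a therapy difference it still moved from 1.43–1.93 to 1.24–1.32 on adjustment, so it solves the second problem but not the first. The simulation contains no feedback from evolving consciousness to therapy, so it does not measure bias from that source.

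**The case against.** The strongest reply is that the primary models do not contain the covariate. Every section that writes out a recovery model omits treatment, and the DAG rule, applied as written, would screen therapy time out. The article is also condensed, and a fuller document may say which model carries the time-dependent terms. Mortality is analysed by Cox regression, functional scores by mixed models or GEE, and a cause-specific model is a planned sensitivity analysis; none of these needs a value after death. This stands as far as it goes: it limits the Fine-Gray problem to the Fine-Gray models and makes bias in the primary estimate conditional. It does not remove the contradiction, because the treatment rule is unqualified and the Discussion repeats it.

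A second reply is that care is described as standardized, so therapy may not differ by baseline level. That is possible, and adjustment would then leave the exposure estimate essentially unchanged. But the plan measures intensity per modality at every visit, and makes hyperbaric oxygen depend on indication and availability, so it does not treat intensity as constant.

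A reader might infer more: that the primary VS/MCS estimate will be biased, that the bias runs towards the null, and that 1.06 is the expected result. The article does not support this. It does not say that MCS patients receive more therapy than VS patients, and if they received less the shift would go the other way. The 1.06 is one assumed scenario among several. Nor is it right to call the Fine-Gray coefficient meaningless. The model can be fitted under a convention such as last value carried forward; the criticism is that the convention is unstated and arbitrary, and that the link to cumulative incidence is lost.

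**Conclusion.** The concern holds in conditional form. The contradiction is certain and rests on the text alone. If therapy time enters the Fine-Gray models, two consequences follow without any numerical assumption: a value after death has to be invented, and the VS/MCS estimate answers a different question from the one under Study objectives. The claim that covariate adjustment isolates the natural course is not supported.

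The size and direction of any shift in the primary estimate are unknown. Under the assumptions shown, a total HR of 1.30 could stay at 1.30 (no therapy difference), fall to about 1.06 (60 min/week more in MCS) or rise to about 1.59 (60 min/week less in MCS). Whether the primary estimate is affected at all depends on which of the two rules the analyst follows.

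**What to change.** - In the Exposure variable section and the Discussion, state that the Fine-Gray models for baseline predictors (Models 1 to 5 and the nested comparison) use baseline covariates only.
- Describe therapy time by VS/MCS group over follow-up, so that readers can see whether it differs.
- Move any treatment question to a labelled exploratory analysis outside Fine-Gray with a stated estimand. Examples are a cause-specific or landmark model with lagged therapy time; marginal structural weighting is one option.
- Drop the claim that adjusting for therapy time isolates the natural course.

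The cost is wording in two sections; data collection and patient care do not change. The downside is that the headline result can no longer claim to separate natural course from treatment effect.
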